##### Opinions and General Knowledge of Medical Experts About a Vegan Diet and Dietary Supplements (For a Vegan Pregnancy, Infancy and Early Childhood) Should Be Established

The impact of expert opinion and knowledge on a vegan diet regarding their advice on DS for vegans (during vegan pregnancy, infancy and early childhood) should be clarified. Statistically evaluated results of the survey should allow conclusions about the influence of information supply by medical experts on nutrient supply, of vegan pregnant women and growing children (up to the age of 5 years). A possible misinterpretation of the health risk of a vegan diet during pregnancy, infancy and early childhood due to insufficient knowledge of DS could increase health risks.

A negative basic attitude towards a vegan diet influences the relationship of trust between vegans and their physicians. If there is no advice on DS, health risks can increase.

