
Previous studies that investigated vegan diets during pregnancy and early childhood focused either on medical risks or aspects such as parents’ knowledge about a vegan diet or DS intake. Kostecka et al. [33] found that parental food and nutritional health literacy plays a central role in ensuring safe vegetarian diet for children, especially regarding the correct use of DS. Palma et al. [5], Sebastiani et al. [7] and Papadopoulou et al. [45] show that a well-planned vegan diet can be suitable during pregnancy. However, careful medical monitoring of micronutrient intake is necessary, which highlights the importance of advice from medical experts. Nevertheless, these studies do not fully consider the social and behavioral factors that can influence parental decisions. The VedieS study addresses these gaps by investigating how external factors (e.g., criticism from medical experts, lack of advice, use of non-professional information sources) influence dietary behavior and DS use among pregnant vegans and parents of vegan children. A study by Bivi et al. [34] showed that many vegan parents reported that they do not feel sufficiently supported by their pediatricians. Instead, many relied on online platforms (e.g., social media) or advice from peer groups to decide whether to take or administer DS. The VedieS study aims to examine how factors such as trust in expert advice, perceived barriers regarding effectiveness of DS, and social expectations can influence vegans’ adherence to supplementation recommendations and maintenance of their diet during sensitive life stages such as pregnancy and childhood. Furthermore, little is known about medical experts’ perspective on this issue. A recent study from France [46] found that many pediatricians and dieticians feel unprepared to advise vegan families. Some even have negative attitudes toward a vegan diet. By including both vegan participants and medical experts in our survey, we want to examine whether such attitudes lead to less effective counseling, inconsistent advice, lower patient trust and consequently to possible health risks. Understanding these connections is important to improve communication and to provide reliable, competent support for vegan parents and pregnant women. Previous research has primarily focused on food and nutritional health literacy or the medical impact of a vegan diet. Our study is one of the first to examine how social environment, information sources, and trust in medical experts influence DS use and dietary behavior in vegan families during pregnancy and early childhood. The findings can help explain behavior patterns and support medical experts in their advisory role.

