#### 2.1.1. Primary Objectives

##### Determination of Main Influential Factors That Affect Vegans Regarding Their Diet During Pregnancy and When Feeding Their Children (Up to the Age of 5 Years)

Influence by medical experts or other influences (e.g., social environment, Internet and social media, magazines) concerning the decision for or against a vegan diet should be clarified. Depending on the source of information, the possible risks of a vegan diet during pregnancy, infancy and early childhood can be misjudged.

The identification of information sources for vegans on dietary supplements, as a reason for the approval or rejection of DS (during pregnancy, infancy and early childhood), embodies trustworthiness by ranking.

It should be determined which information on DS (during pregnancy, infancy and early childhood) is used and whether this information appears trustworthy or causes uncertainty. Information received affects selection, intake, or avoidance of certain DS. The health impact of selected sources of information on DS can be made visible. Medical expert advice and other opinion-forming aspects (e.g., social environment, Internet and social media, magazines) should be ranked according to their relevance. Main sources of information should be identified.

This can be an important approach for the improvement of information supply on DS in a vegan diet and for minimizing risks preventively. By recognizing sources of information classified as the most important for vegans, the main causes of frequent inadequacies in the provision of information could be identified and if necessary, positively changed.

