### 2.2. Study Design

The VedieS study is an explorative, cross-sectional study. Two quantitative online surveys on a vegan diet and the intake of DS during pregnancy, infancy and early childhood (up to the age of 5 years) are carried out: The first survey focuses on vegans (parents and pregnant women) and the second survey on medical experts (pediatricians, gynecologists, general practitioners, pharmacists, dieticians). Each survey will take approximately 20–25 min to answer.

Recruitment for the survey is scheduled to take place between October 2023 and the end of July 2025. There is no survey restriction to Austria. Participants from Germany, Switzerland and Italy/South Tyrol, Liechtenstein, and Luxembourg (or other EU countries) can also answer the questionnaires and will be included in the evaluations. Since the survey is conducted in German, the survey refers to participants who understand the German language.

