### 2.9. Data Security

Survey data is collected using the online survey tool LimeSurvey. Participants who want to take part in the scientific survey follow a link/URL that takes them to the survey. All anonymous data will be transferred from LimeSurvey to EXCEL (Microsoft Corp., Redmond, WA, USA) and further to R version 4.5.1 (R Core Team) and IBM SPSS Statistics version 31 (IBM Corp., Armonk, NY, USA) for processing and statistical evaluation. Data that are in the stage of statistical analysis and evaluation will be stored at the u:cloud storage system of the University of Vienna (protected server). Access to the LimeSurvey Cloud instance and u:cloud storage system will only be possible by password personalized for the principal investigator (PI) and study directors. No names of participants will be asked or recorded. Only answered, anonymized questionnaires will be stored until final analysis and publication of data at the LimeSurvey cloud instance and the u:cloud storage system.

Participation in the survey is voluntary and can be canceled at any time. The survey tool LimeSurvey processes survey data completely anonymously. LimeSurvey is an international survey tool, but the protected server where survey data is hosted (saved at the LimeSurvey Cloud instance) is located in Germany. Data about names, Email or IP-addresses are not saved. Collected data is protected by the consent of the General Data Protection Regulation (GDPR). LimeSurvey guarantees full EU GDPR compliance because of the selection of the German server as server location. Survey/response data is stored in a separate database with a separate username/password for each LimeSurvey Cloud instance. The connection of the used browser to LimeSurvey servers is also encrypted using SSL (Secure Sockets Layer) which is known to be the standard technology for securing Internet connections and protecting sensitive data. The connection is encrypted, which ensures protection, security and anonymity for participants and their personal data. The data received will be treated confidentially and processed and evaluated exclusively for scientific purposes. The link/URL for the survey will remain accessible for approximately 2 years (July 2023–July 2025).

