
Research gaps concerning the administration of DS, the consistency of taking them and compliance shall be closed by statistically evaluating data from performed surveys (vegans, pediatricians, gynecologists, general practitioners, pharmacists, and dieticians). In addition, causes for the intake or rejection of DS (from a social and socio-demographic perspective) are to be examined. Resulting risks concerning the supply of nutrients are to be determined as well as the role that information sources play in this context. It is precisely these unanswered questions that underline the relevance of the VedieS study, as they are directly related to risk prevention. According to a recent study by Meulenbroeks et al. [61], pregnant women following a vegan diet often receive limited or no specific dietary guidance from obstetric healthcare providers. Only 19% of participants reported having received nutritional counseling that was specific to their needs during pregnancy. The VedieS study’s approach to identifying the cause of nutrient deficiencies during vegan pregnancy and childhood, due to a fundamental lack of information, is new and can be important for preventing health risks for vegans. Unsupplemented vegan pregnancies are associated with a higher risk of adverse outcomes [45]. These findings highlight the importance of guideline-based supplementation for vegans during sensitive life stages. The quality of the information sources used by vegans is most likely dependent on the existing attitude of the information providers. If medical experts have a negative attitude towards a vegan diet and DS, their advice may be inadequate—either due to a lack of knowledge about a purely plant-based diet, or because a vegan diet is discouraged per se without providing additional information. Knowledge gaps regarding vegan diets remain common among medical experts, likely due to limited nutrition education and a lack of familiarity with plant-based dietary patterns [44,60]. As a result of limited professional support, many vegan pregnant women turn to alternative sources of information such as books, online platforms, or peer communities to address their specific dietary needs [61]. It is important to know exactly where the information received comes from in order to be able to draw conclusions about its safety and reliability. In a cross-sectional online survey by Fuschlberger et al. [62] among Austrian vegans, 92% reported taking vitamin B_12_ through DS or fortified foods, yet fewer than 10% had consulted a medical expert. However, more research is needed to find out exactly which specific sources of information are being used.

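### The objectives promise conclusions about experts' influence on nutrient supply, health and deficiency, but two unlinked, anonymous, cross-sectional surveys support only associations among self-reports

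*Protocol article*

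**What the plan says.** Four places in the protocol article promise more than a description of answers.

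- Section 2.1.1, objective on medical experts' opinions and knowledge: "Statistically evaluated results of the survey should allow conclusions about the influence of information supply by medical experts on nutrient supply". The same objective states as a fact that "A negative basic attitude towards a vegan diet influences the relationship of trust between vegans and their physicians".
- Section 2.1.1, objective on main influential factors: "The health impact of selected sources of information on DS can be made visible".
- Section 1, giving the reason for surveying both groups: "we want to examine whether such attitudes lead to less effective counseling, inconsistent advice, lower patient trust and consequently to possible health risks".
- Section 4, describing what is new about the study: "approach to identifying the cause of nutrient deficiencies during vegan pregnancy and childhood, due to a fundamental lack of information".

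On design, section 2.2 says: "The VedieS study is an explorative, cross-sectional study". It describes two online questionnaires, one for vegan parents and pregnant women and one for five professions. Section 2.9 adds that "The survey tool LimeSurvey processes survey data completely anonymously" and that names, email addresses and IP addresses are not kept. Section 3.1 bases all findings on how often answers were given.

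**The concern.** Each promise is a causal statement. It runs from what experts think or say to what patients trust, take or lack. Supporting it would require three things: experts' attitudes joined to the patients they advised, a measure of nutrient supply or deficiency, and some basis for the order of events. The article describes none of these, and section 5.2 does not list their absence among the limitations.

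What is at stake is the reach of the study's conclusions. If the objectives stay as they are, frequencies from the expert survey could be set beside frequencies from the vegan survey and read as links in one chain. The readers would be clinicians and families making decisions about pregnancy and early childhood.

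**Working it through.** No formula applies, so the check sets the promises against the design, the data and the planned comparisons.

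**The plan's own figure.** The only derived number is the vegan target in section 2.6.1. At the upper bound, 400,000 births × 1% = 4000 families, and 25% of 4000 = 1000, as stated. At the lower bound, 400,000 × 0.5% = 2000, and 25% of 2000 = 500. The expert target is 5 × 60 = 300. The point does not depend on these numbers, because more respondents would create neither a link between the surveys nor a nutrient measure.

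**Step 1: linkage.** Section 2.9 rules out names, email addresses and IP addresses. Section 3.2 lists a practice postal code for experts and an urban/rural origin for vegans, so no shared field is listed. Even a shared area code would not tie a patient to the expert who advised that patient.

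**Step 2: planned comparisons.** Section 2.7 lists four comparisons among vegans: rural or urban; supplement users or not; diet changed in pregnancy or not; professional advice or informal sources. It lists three among experts: support or reject vegan diets; advise or discourage supplements; profession. None of the 4 + 3 = 7 crosses the surveys. The section allows further comparisons to be added, but an added comparison cannot supply a missing key.

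**Step 3: nutrient measure.** Sections 3.1 and 3.2 list opinions, information sources, dosage estimates, self-reported compliance, perceived benefits and trust in sources. Nutritional status appears in section 3.1 only as an assumed consequence of supplement decisions. The nearest item is questionnaire category I in section 2.5, which covers deficiency and dosage by self-report. Section 4 itself contrasts the study with earlier work on clinical or biochemical outcomes.

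**Step 4: direction.** Each respondent answers once. Section 1 reports that many parents hide a child's vegan diet from the pediatrician to avoid criticism. On the article's own account, then, a family's earlier choices can shape its contact with experts. The covariates in section 2.7 (age, gender, education, household situation, profession) do not settle which came first.

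**Step 5: what can be estimated.**

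| Question | Source | Estimable? |
|---|---|---|
| Experts' attitude and knowledge versus the advice they report | Expert survey | Yes, as an association |
| Respondent-reported advice, attitude and trust versus self-reported supplement use, diet change or deficiency | Vegan survey | Yes, as an association, if the items are asked |
| Expert-reported attitude versus patients' trust, supplement use or supply | Needs both surveys linked | No |
| Effect on measured nutrient supply or deficiency | Measure not among the outcomes | No |

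**The case against.** The strongest reply is that the article is modest about its methods. It calls the study descriptive and exploratory, disclaims a hypothesis-testing design, reports p-values descriptively and concedes self-report error. Much of the disputed wording is hedged, and two of the four statements stand in the Introduction and Discussion rather than in the objectives. Supply may also be meant loosely: the compliance objective in section 2.1.2 uses the word for how well users are provided with the supplements they take.

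Part of this stands. It shows that the analysis plan is not itself overreaching and that the fault lies in the wording. It does not remove the conflict. Two of the statements are in the primary objectives, and the Discussion's claim about the cause of deficiencies is not hedged. A study that describes itself as descriptive is harder, not easier, to square with those promises.

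A reader might go further and infer that nothing in section 2.7 can relate expert attitude to trust or supplement use. The documents do not support that. The section plans logistic regression on supplement use and a comparison of professional advice with informal sources, and section 3.2 collects trust in advisory sources and reasons for diet change. Attitude as the respondent perceived it can therefore be studied within the vegan survey. Within the expert survey, opinion can be related to advice, which serves part of the same primary objective and part of the aim in section 1.

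A reader might also conclude that deficiency goes unrecorded. The questionnaires are in a supplement that is not shown, and category I may record it by self-report. Only the absence of an objective measure among the stated outcomes can be asserted.

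**Conclusion.** The concern holds as a mismatch between the stated objectives and the design. The effect of expert-reported attitudes on patients' trust, supplement use or nutrient supply cannot be estimated, and causal direction cannot be established for any of the promised effects. The associations within each survey are unaffected.

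No numerical bias can be attached to this. A reader might try to size it as a contrast of five profession averages, but no such analysis is planned. The size is best stated as scope: two passages in the primary objectives and one aim each in the Introduction and Discussion claim more than the data can show, and none of the seven listed comparisons joins the surveys.

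The conclusion rests on two assumptions: that the unseen questionnaires contain no linking key, and that they contain no objective intake or laboratory measure beyond what the article lists. It is a correction to wording that changes what the study may conclude. It does not invalidate the surveys, and that the final report will overclaim is a risk, not something the documents show.

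**What to change.** 1. Restate the two passages in section 2.1.1, and the aims in sections 1 and 4, as two questions:
   - (a) Within the expert survey, how are attitude and knowledge associated with the advice reported?
   - (b) Within the vegan survey, how are respondent-reported expert advice or attitude, and trust, associated with self-reported supplement use, diet change and any self-reported deficiency?
2. In those places, replace nutrient supply, health impact and the cause of deficiencies with self-reported supplement use and self-reported or perceived deficiency. Word the sentence on trust in section 2.1.1 as a question rather than a fact.
3. Add three limitations to section 5.2: the two surveys are not linked and are compared only side by side; nutrient status is not objectively measured; and reverse causation cannot be excluded.

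The cost is more modest claims. No new data are needed, and the sample targets and the analyses in section 2.7 stay as they are.

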#### 2.1.2. Secondary Objectives

##### Determination of the Level of Knowledge of Vegans on Dietary Supplements, Nutrient Deficiency Risks and Correct Dosage of Dietary Supplements During Pregnancy, Infancy and Early Childhood (Up to the Age of 5 Years)

If the risk of incorrect dosage of DS is misjudged by vegans during pregnancy, infancy and early childhood, nutrient deficiencies or overdose with DS become likely. Risks of nutrient deficiency due to missing intake or incorrect selection of DS because of a lack of food and nutritional health literacy should also be cognizable. Avoiding these circumstances would require a competent information provision for vegans by medical experts (pediatricians, gynecologists, general practitioners, pharmacists, dieticians). Imprecise advice could affect the relationship of trust between medical experts and vegans as well as the nutrient supply during pregnancy, infancy and early childhood.

